### Study Setting

The study is conducted mainly though internet, using 3 main tools:

The specifically designed GRASP platform
The *Qualtrics* survey service licensed though Columbia UniversityThe Google Suite platform as an email service to contact candidates and attend to the private questions and concerns of the study participants.

In addition, the samples were received through traditional mail in the EC Headquarters in Barcelona, where they were initially processed and identified. The samples were then transported to the EC laboratory at the Hospital del Mar Research Institute (IMIM), second floor, to be analyzed using the techniques described below. The research team worked at both the EC headquarters and the IMIM laboratories. During the COVID-related lockdown that was established in Spain in March 2020, the laboratory analysis was interrupted for 3 months.

The usability of the platform and the multiple automated processes, such as *sending an email with a specific link to a questionnaire*, and the logic pathways (adaptive questioning) and validation requirements used in the *Qualtrics* questionnaires were systematically tested by the research team. A checklist of all possible scenarios was devised, and they were all executed by a blind research team member and the principal investigator. Once errors were identified, they were corrected, and the process was repeated from the beginning. In addition, participants were encouraged to report any problems or ideas to improve the procedures, so changes could be implemented when needed during the study.

### Participants

All the participants were correctly and fully informed by writing (refer to the participant information sheet in Multimedia Appendix 1) and prompted to ask any questions by email. In that case, answers were provided until the candidate confirmed that they had no more questions and were satisfied with the information received. All participants indicated their agreement to participate and signed an informed consent (IC) form (Multimedia Appendix 2) that was sent to the project email address and checked by the principal investigator before inclusion. It was not possible for candidates or participants to answer any online questionnaires without previously receiving the specific link, which was sent by the research team only when the participant met the criteria to fill the questionnaire. Participants were asked to sign with their online usernames to further protect their physical identity, as recommended by Barratt et al [21,25]. Participants received no monetary compensation for their participation, but instead, they were offered the possibility to get the NPS they reported on analytically tested for free in the EC laboratory, located in the *IMIM*, Barcelona. The cost of this service is US $110 if contracted independently through the EC International Drug Checking Service.

This study included e-psychonauts, who have been defined as people with the following characteristics:

Previous experience with at least three NPS 12 months before the study inclusionActivity on online communities where NPS consumption is discussed.

The inclusion and exclusion criteria for participants are provided in Textbox 1.

Inclusion and exclusion criteria for participants.
**Inclusion Criteria**
Meeting the operational definition of e-psychonautBeing 18 years or older at the time of recruitmentSelf-reported plans of maintaining the use of new psychoactive substances for the following 18 months
**Exclusion Criteria**
Difficulties in communicating in EnglishDifficulties in using new technologies to participate in the studyPotentially pregnant womenPotential presence of severe psychopathological symptomatology

Note that there is no restriction on the geographical location of the participants, as the study will not collect such data to further protect the participants’ physical identity. Therefore, participants from around the globe could participate in the study. Both inclusion and exclusion criteria have been mainly assessed by direct self-reporting in an initial screening questionnaire (Q0), except the following:

Previous participation in forums has been assessed by self-report and exclusive advertisement of the study on these forums.Difficulties in using new technologies have been assessed by the steps required to complete the screening process, such as sending an IC form in a particular format, registering to the platform, and following the instructions there to introduce themselves to the research team and other participants.Difficulties in communicating in English and the presence of potential psychopathological impairments have also been evaluated by the principal investigator, assessing the answers to long and elaborate open questions in the screening questionnaire (Q0) and in the written introductions to the online platform.The potential of being pregnant was assessed by indirect questioning using the same screening questionnaire (Q0) questionnaire.

### Recruitment

Recruitment ads were sent to the moderators of the selected online communities after establishing bilateral communication with them, mainly to ask permission and explain the goals of the project. To maximize interest in participating in the study, the only focus was on establishing rapport with community leaders, as if they share their interest in the study, they will be able to transfer it to the rest of the community [31]. Each community moderator posted the research ad in the most appropriate way in their community after discussing it with the research team. Research ads were posted on all communities during the summer of 2019 (refer to Multimedia Appendix 3 for details). The recruitment was designed to be sequential until the designed sample size was reached or the study reached its duration limit.

The operational definition for online communities of people who use NPS has been adapted from the study by Barratt [21]:

Surface websites with at least 5 years of existencePresence of participation forums dedicated to discussing the use of NPSAt least weekly activity on the community forumThe use of pseudo-anonymity by community members to identify themselvesThe presence of official and analytical drug checking services in the community.

When the study design was completed (October 2018), there were 4 communities meeting the previously stated criteria [21]:

*Bluelight* [32]: Established in 1997, bluelight is probably the most prominent community of people who take illicit drugs, with approximately 250,000 members. Within the community, there is a subdivision in which the use of NPS is exclusively discussed. The community is known for its commitment to promoting risk management and harm reduction strategies among its participants as well as its formidable contributions to similar research projects [28]. Registration is required to access the content.*Reddit* [33]: Established in 2010, this subreddit community allows almost any type of discussion regarding NPS. The community has approximately 90,000 members, but it is part of a broader community of people who use illicit drugs (not only NPS), with over 700,000 members. Both of these are part of the global reddit community, where all types of topics are discussed. The platform does not require registration to access the content.*Drugs-forum* [34]: Established in 2003, this community also seems to have approximately 250,000 members. Registration is required to access the content.*DNstarsVIP*: Established after discussing about NPS sources was banned on the *reddit* community, *DNstars* is a strongly emerging community with approximately 2000 users. Registration is required to access the content.

The main communities that were assessed and excluded were as follows:

*Legal-highs forum*: excluded because of the lack of weekly interactions, technical website problems, and impossibility to contact community managers.*Erowid*: excluded because of the lack of an active forum.*Psychonaut wiki*: excluded because of the lack of an active forum.*Tripsit*: excluded because of the lack of an active forum, although there was an internet relay chat–supported chatroom.
*Dimethyltriptamine-nexus:* excluded because of the lack of a specific NPS subsection.
*Ecstasy data*: excluded because of the lack of an active forum and the lack of a specific NPS subsection.*Shroomery:* Excluded because of the lack of a specific NPS subsection.

To the best of the authors’ knowledge, the selected communities were the main ones at the moment when the selection occurred (October 2018), although it has to be acknowledged that this is a rapidly changing scenario; in a few years, this same process might produce different outcomes. At that moment, the authors were unable to find any contradicting information with that assumption. Soussan et al [35] referred to *bluelight*, drugs-forum, and legal-highs forum as the top 3 communities. However, they did not consider collaboration with drug checking organizations to be a relevant factor. Moreover, as stated above, these rankings are expected to change over relatively short periods [35].

The GRASP platform, which allowed for interaction among participants themselves and with the research team, was the main tool to promote participant engagement and minimize dropout rates.

### Sample Size

In the most recent review consulted by the authors, the sample sizes reached with web-based questionnaires in people who use illicit drugs ranged from 80 to 9867 [36]. The expected losses while filling these types of questionnaires are about 50% of the sample, but the authors have not found other online longitudinal studies including questionnaires like this one. According to the aforementioned review, the authors expected 80 candidates as the best possible estimate to achieve 40 final participants. Assuming that each participant takes one NPS every month during the duration of the study, the expected number of registered self-administration trials of NPS would be 480. As the study has been designed as exploratory, the sample size could not be determined based on the needs to perform specific statistical tests.

### Study Procedures and Timeline

The study’s internal timeline and workflow are graphically represented in Multimedia Appendix 4. The first recruitment effort consisted of online discussions with forum moderators and posting the institutional review board (IRB)–approved announcement for candidates (displayed in its entirety in Multimedia Appendix 3) in those forums. In the announcement, potential candidates were instructed to send an email from a secure and nonidentifiable address to the research team ([contact]). Candidates were then informed more broadly about the study. Candidates were informed homogeneously by sending the IRB-approved *information for candidates’ sheet* to their email (the sheet used in this study can be found in Multimedia Appendix 1). The principal investigator then offered the candidates to answer any questions that might have arisen after reading the participant information sheet. When the participants had read and discussed the given information about the study with the principal investigator, they were asked to register on the GRASP platform and send the IRB-approved IC form, completed with the registered username to the study email. In Multimedia Appendix 2, the IC form is available for consultation. Finally, the candidates were asked to complete the screening questionnaire (Q0) and introduce themselves on the platform without providing information that might reveal their real-world identities. When all these processes were complete, the principal investigator checked the IC form, the screening questionnaire, and the platform introduction to assess if the participant met the inclusion or exclusion criteria. Candidates were then informed by email about the results of the assessment, thus either being rejected or accepted as participants.

Once participants were accepted, they could interact with other participants on the online platform and received detailed instructions on how to conduct the study. However, NPS sourcing and the effects of the substances included in the study were not allowed. In case of a severe protocol violation such as this one, participants were immediately removed from the study and their information was deleted. In case of minor protocol violations, participants were notified and given the opportunity, if applicable, to amend their noncompliant behavior.

The first mandatory step was to fill a sociodemographic and drug use history questionnaire (Q1). This questionnaire was available to each participant through a participant-specific link, which was sent by email once they were accepted. After that, participants were asked to fill the sample submission questionnaire (Q2), where information about the sample they intended to consume was asked. This questionnaire was then reviewed by the principal investigator and approved if the substance met the study criteria of being a new psychoactive substance. The samples that did not meet the inclusion criteria were not accepted, and the participant was notified by email. The sample submission questionnaire (Q2) was available to all accepted participants as a link on the platform. All the questionnaire answers were reviewed weekly by a member of the research team to communicate to the participant the acceptance of the sample and to mark them as valid or invalid data for later analysis.

If the sample was approved, the participant received a specifically generated sample code with the instructions to send a small amount of the sample (approximately 30 mg, usually below the psychoactive threshold) via traditional mail to the laboratory at the IMIM. The sample was analyzed there, and the result was sent back to the user, along with harm reduction advice when appropriate.

Meanwhile, the users could consume the substance whenever they decided, as the study was intended to be observational. However, most of the participants waited until they had the result of the laboratory analysis to proceed with the self-administration trial. The self-administration trial started with the users filling the drug effect baseline questionnaire (Q3a), and then, they consumed the reported substance and filled the drug effect questionnaire (Q3b) 24 hours after filling the baseline questionnaire (Q3a). The links to these questionnaires were available for all participants in the forum, and the veracity of the information was ensured by asking information only available to each participant, such as the sample code of the reported sample.

Study recruitment began in August 2019 and is still ongoing. In August 2020, the first participant concluded the 1-year follow-up.

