**Methods:**

To cover this purpose, we designed a highly personalized, observational longitudinal study methodology. Participants will be recruited from online communities of people who use NPS, and they will be followed online by means of a continuous objective and qualitative evaluation lasting for at least 1 year. In addition, participants will send samples of the substances they intend to use during that period, so they can be analyzed and matched with the effects they report on the questionnaires.

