**Results:**

The research protocol was approved by the Institutional Review Board of the Hospital del Mar Research Institute on December 11, 2018. Data collection started in August 2019 and was still ongoing when the protocol was submitted (September 2020). The first data collection period of the study ended in October 2020. Data analysis began in November 2020, and it is still ongoing. The authors expect to submit the first results for publication by the end of 2021. A preliminary analysis was conducted when the manuscript was submitted and was reviewed after it was accepted in February 2021.

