As it is an exploratory study, the data analysis procedures will be mainly descriptive statistics, to maximize an adequate visualization of the data collected within the minimum space. In addition, as there is no control group, statistical tests will be limited to potential comparisons to assess bias on the results, such as comparing data from participants who complete the study with participants who drop out or are excluded. However, no statistical corrections will be applied to adjust the representativeness of the sample, as this validation will be done by comparing the sociodemographics of the study sample with the characteristics of the population of psychonauts widely reported in the literature. Statistical tests might also be used to compare information from the initial questionnaire Q1 and the data from the follow-up questionnaire Q4. The nonparametric Wilcoxon signed-rank analysis will be used to perform a mean comparison of the quantitative data and the chi-square test for qualitative data. In addition, factor analysis will be attempted to study the relationship between all the visual analog scales used to assess the subjective drug effects.

The data analysis will focus on the outcomes of the participants who completed the study. Data entries containing evident errors or inconsistent information will be discarded, and the extent to which this might have impacted the results will be reported.

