## Results

The research protocol was approved by the IRB of the *IMIM* on December 11, 2018. Data collection started in August 2019 and was still ongoing when the protocol was submitted (September 2020), finalizing in October 2020.

Data analysis began in November 2020, and it is still ongoing. The authors expect to submit the first manuscript with preliminary results by the end of 2021.

From a total of 182 screened candidates, only 17 (9.3%) completed at least one self-administration trial, resulting in a total number of 64 self-administration trials. From these, 40 different substances were analyzed.

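### Within a collection period ending in October 2020, participants accepted after October 2019 cannot reach the one-year questionnaire, and the completer/dropout comparison has no place for them

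*Protocol article*

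**What the plan says.** **Length of follow-up.** The Abstract (Methods) says participants will be "followed online by means of a continuous objective and qualitative evaluation lasting for at least 1 year". The second amendment, submitted in November 2019, lengthened participation from six months to one year and lowered the minimum age from 21 to 18. Under Questionnaires, Q4 is the one-year follow-up instrument.

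**Recruitment.** Study Procedures and Timeline says "Study recruitment began in August 2019 and is still ongoing. In August 2020, the first participant concluded the 1-year follow-up". The Recruitment section places the advertisements in summer 2019. It ends recruitment when the target size or the limit on study length is reached, and sets no last entry date that would leave room for a full year.

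**Close of data collection.** According to the Results section, data collection "was still ongoing when the protocol was submitted (September 2020), finalizing in October 2020". The Abstract words it differently: "The first data collection period of the study ended in October 2020". Both say that analysis began in November 2020.

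**Analysis.** Data Management and Statistical Analysis says the analysis will centre on people who finished the study. Statistical tests are limited mainly to checks for bias, such as "comparing data from participants who complete the study with participants who drop out or are excluded". A comparison of Q1 with Q4 is mentioned as a possibility.

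**The concern.** A one-year follow-up, recruitment still open about 13 months after it began, and a close in October 2020 do not fit together. Late entrants run out of calendar time whether or not they stay engaged. The analysis section names completers on one side and dropouts or exclusions on the other, and a participant whose year was interrupted by the close belongs to neither.

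Three things are at stake.

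- **The bias check.** If truncated participants are put with the dropouts, administrative cut-off is mixed with real loss, and the comparison becomes partly one of early against late entry. If they are left out of both groups, they disappear from the check.
- **The Q1 to Q4 comparison.** It can describe only people who entered in the first weeks of the study.
- **Feasibility.** Whether this design can collect reliable data is one of the three research questions. Without person-time, a low yield of trials cannot be separated into weak engagement and short observation.

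Entry date is also tied to who was eligible, because 18- to 20-year-olds could join only under the later amendment.

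**Working it through.** **1. The plan's own figures.** The Sample Size section gives 80 candidates, about 50% losses, 40 final participants, one substance per month and 480 expected trials.

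- 80 × (1 − 0.5) = 40.
- 40 participants × 12 months × 1 per month = 480.

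Both reproduce exactly. The 480 therefore assumes a full 12 months for every final participant.

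**2. Last entry date that allows one year.** Last entry = close − 12 months. The day of the close in October 2020 is not given, so the last entry date lies between 1 and 31 October 2019. Taking the later close, 31 October 2020, the longest possible follow-up is:

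| Accepted on | Months available |
|---|---|
| 30 November 2019 | 11.0 |
| 31 January 2020 | 9.0 |
| 30 April 2020 | 6.0 |
| 30 September 2020 | 1.0 |

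**3. A group that needs no accrual assumption.** Participants aged 18 to 20 could be admitted only under the amendment submitted in November 2019. That is after the last entry date, so none of them can reach Q4 by October 2020. The extension to one year is in the same amendment, so everyone who could complete by the close had entered before it was submitted.

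**4. Share of entrants who could complete.** The article gives no acceptance dates, so this step rests on assumptions.

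*Even entry, from August 2019 until some date in August to October 2020.* Share = (last entry − start) ÷ (end of recruitment − start).

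- Most favourable: start 1 August 2019, close 31 October 2020, recruitment to 31 August 2020. 91 days ÷ 396 days = 0.230.
- Least favourable: start 31 August 2019, close and end of recruitment both 1 October 2020. 31 days ÷ 397 days = 0.078.

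About 8% to 23% could reach one year, so about 77% to 92% could not. Mean possible follow-up, capped at 12 months, is about 6.5 to 8.2 months (6.48 and 8.16 before rounding). At one trial per month, 40 participants would give 40 × 6.48 ≈ 259 to 40 × 8.16 ≈ 326 trials, against 480.

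*Early entry.* If everyone was accepted by about 22 September 2019, all could complete and the 480 is unchanged.

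**5. Reported yield.** The Results section gives 64 trials from 17 people, or 64 ÷ 17 ≈ 3.8 each. No person-months are given, so this cannot be set against the planned rate of one per month.

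**The case against.** The strongest reply has five parts.

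- **Classification.** A reader might infer that late entrants will be counted as dropouts and that the dropout rate is therefore overstated. The article does not say so. They could equally be left out of both groups or followed further. This part of the reply stands.
- **Finality of the close.** A reader might infer that collection stopped for good in October 2020. The Results section reads that way, but the Abstract's reference to a first period leaves room for later follow-up. The statement that recruitment continues probably dates from the September 2020 submission, with the October close added afterwards. Part of the conflict may thus be unrevised text. This stands as a reason to reconcile the passages. It does not remove the problem, because recruitment described as open at about that time was open long after October 2019.
- **Number affected.** Advertisements ran in summer 2019, so most or all entry may have been early. This stands: no single percentage can be defended.
- **Main outcome.** The difference between Q3b and Q3a is measured within a trial over about 24 hours and does not need a year of follow-up. The study is exploratory and mainly descriptive, and the Q1 to Q4 tests are optional. This stands, and it limits the damage.
- **Condensed article.** Definitions of completer and dropout, and the detailed timeline, may sit in the full protocol or in appendices that are not shown. This stands only in part. The article itself chooses the completer focus and names the comparison groups, and those groups do not fit the dates that it also gives.

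**Conclusion.** The point holds in a limited form. With one year of follow-up and collection ending in October 2020, participants accepted after October 2019 cannot complete within that period. The stated comparison groups give them no valid place, and a Q1 to Q4 change would describe early entrants only. For anyone aged 18 to 20 admitted under the amendment, this follows from the dates alone.

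The size is unknown. It runs from nobody, if entry was early, to roughly 77% to 92% of entrants, if entry was even. The upper range is an assumption about accrual and not a finding. The documents do not support the claims that these participants will be counted as dropouts, that follow-up has finally closed, or that the main within-trial outcome is biased by the close. The weight is moderate: it affects the attrition check, the Q1 to Q4 comparison and the reading of feasibility in an exploratory study.

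**What to change.** First, reconcile the Abstract, Study Procedures and Timeline, and Results on whether recruitment and data collection have ended, and state the last acceptance date. Then take one of two routes.

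1. **Keep Q4 open** until each accepted participant's 12-month date. For entry by October 2020 this ends by October 2021, before the submission of first results planned for the end of 2021.
2. **Restrict by possible follow-up.** Limit the completer/dropout comparison and the Q1 to Q4 analysis to participants with at least 12 months between acceptance and the close. Report the rest separately as administratively censored.

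Under either route, keep all valid Q3a/Q3b trials whether or not the participant completed the year, and report trials per participant-month for everyone.

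The cost is small: a survey link left open, or a flag computed from the acceptance date. The downside is a later lock of Q4 under the first route, or a smaller completer/dropout set under the second.
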